**Fig. 3 Fig3:**
[figure not shown]
SPIRIT figure for study protocols

### Data management

Data management (collection, recording, and storage) complies with the rules of ECU Human Research Ethics Committee (HREC) and is reported on annually (ID 15362:[name]). All data has been de-identified and stored according to HREC policy in access restricted, secure repositories.

### Statistical methods

The computer software package IBM SPSS Statistics for Windows version 25.0 (Armonk, NY: IBM Corp) will be used to access the data set and perform the statistical analyses. For the basic online evaluation questionnaire, general descriptive analyses including frequency data with appropriate plots and cross-tabulations will be used to explore and summarise outcome variables. Continuous demographic and baseline characteristics will be summarised using standard statistics (mean and standard deviation) and non-parametric statistics (medians and inter-quartile ranges) where appropriate. Independent *t*-test for normally distributed data, and Mann-Whitney U test for non-normal data, will be used to assess differences between the groups. Frequencies and percentages will be reported for categorical variables and Chi-square test will be used to test for differences in proportion between the groups. The magnitude of change both within and between the intervention and control groups will be assessed using mixed-model ANOVA. Furthermore, changes within the intervention group will be assessed across three time points IT1, IT2 and IT3 using repeated-measures ANOVA. To account for multiple outcomes, the Benjamini-Hochberg correction (i.e. false discovery rate) will be applied to the raw *p*-values. Participants with missing value for the variables of interest (either outcome or predictor) will be removed from the repeated-measures ANOVA models. Specific demographic factors of interest (including but not limited to, gender, age, education, BMI and employment) will be adjusted for in all models. Statistical significance will be indicated at the 10, 5 and 1% level. Cohen’s effect sizes will be provided as a measure of practical/clinical significance and to assist in the interpretation of said ‘statistically significant’ results.

To interpret gut microbiota diversity and to analyse the microbial composition of the gut microbiota, multivariate analysis using a combination of R and PRIMER7 and Permanova+ (PRIMER-E, Plymouth) [82] will be conducted. Principal Coordinates Analysis (PCoA) will be deployed to visualise findings. Distance-based linear models (DISTLM) and distance-based redundancy analysis (dbRDA) will be used to integrate microbiome findings with other relevant data (i.e. dietary intake) that help explain the relationship between the microbiome findings and other outcomes.

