### Primary and secondary outcomes and endpoints

The primary outcome of cooking confidence was evaluated via the theoretical concept of personal beliefs of self-efficacy measured across five areas:
Confidence about being able to cook from basic ingredients;Confidence about following a simple recipe;Confidence about preparing and cooking new foods and recipes;Confidence that what is cooked will “turn out” well; andConfidence about tasting foods not eaten before.

This was performed using the same method as described by Flego et al. [42] by measuring cooking confidence as a proxy for self-efficacy. The questions used were based on works by Short (2003) and Barton (2011) and presented on a 5-point Likert confidence scale ranging from ‘not at all’ to extremely’ confident. This was explored in terms of change over time and between different study groups.

The secondary endpoints were measures of dietary intake, physical activity and mobility levels, body composition, anthropometry, blood, urine and faecal biomarkers of systemic, physical and mental health and are further explained in the sections below. These were also explored in terms of change over time and between different study groups.

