### Sample size

The sample size calculation in this study was based on the findings of the first published quantitative evaluation of Jamie’s Ministry of Food (JMOF) program into its impact on participants’ cooking confidence [42]. Flego et al. reported an increase of > 0.53 on a 5-point Likert scale across all confidence items, which corresponded to a large Cohen’s effect (d > 0.8), whilst no significant changes were observed in the Control group (all *p* > 0.13). Using G*Power, the required sample for a mixed-model analysis of variance test (ANOVA) design (2 groups, each with 2 time points) to detect (conservatively) a small-medium, within-between, interaction effect (Cohen’s *f* = 0.15), at the 5% level of significance and 80% power was 90, or 45 per group. However, Flego et al. [42] noted that the participant retention rate in the JMOF program at T2 was 55% (694 at T1 and 383 at T2). To account for this and to ensure sufficient participation numbers at the end of T2, the aim was to recruit a minimum of 164 participants with 87 in each time-point (i.e. T1 and T2) of the intervention arm. No power calculation to account for T3 samples size was conducted as the investigation was not aiming to detect a change, rather, whether the effect was maintained at T3.

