### Data collection schedule and measures

At all levels of contribution, intervention participants were surveyed at three time points: before the program start (IT1), on program completion (IT2), and 6 months after program completion (IT3). Control participants were surveyed at two time points: 6 weeks prior to program commencement (CT1) and on entry to the program (CT2) (Fig. 1). Computer programmed ‘rules’ automated this process. The ECU SRC ensured consent prior to participation in the study and distributed the online survey assessment using Voxco CATI© Software [47]. The ECU SRC complies with the AMSRS Code of Professional Behaviour and since 2008 SRC has been an ISO20252 standards accredited organisation. All projects undertaken by ECU SRC are conducted in full compliance with the Interviewer Quality Control Australia (IQCA) as recommended by the Australian Market Research Industry and NHMRC/AVCC guidelines on research practices. Postal versions of all documentation were sent to persons who did not have a working email address or access to a computer. The ECU SRC sent participants their online questionnaire 1 week prior to T1, T2 and T3 (for intervention) and if necessary, they received a second reminder email during the week of T1, T2 or T3 as well as a clinic appointment reminder where applicable.

Four levels of contribution were offered to all WA adults registered on the program database (Table 1). The minimum level of contribution, completed by participants at all levels at each time point, consisted of the basic online survey evaluation used in Victoria and NSW [42–45] with the incorporation of additional assessments. These included, quality of life measured using the SF-12® Health Survey [48], wellness using the Subjective Vitality Scale [49, 50] and the Warwick-Edinburgh Mental Well-being Scale (WEMWBS) [51], and physical activity determined using the International Physical Activity Questionnaire (IPAQ) self-administered short-form [52] and the Godin Leisure-Time Exercise Questionnaire [53] (Additional file 1). Those who chose to contribute at level 2 completed the above questionnaire and also attended a clinic appointment at each time point, where they underwent dietary, anthropometric, body composition, blood pressure, timed “Up & Go” [54] and hand grip strength [55] assessments.

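### The two-time-point group-by-time ANOVA is a change-score test that never adjusts for the T1 score. A prespecified baseline-adjusted analysis beside it would show whether the result depends on that choice.

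*Protocol article*

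**What the plan says.** Under Statistical methods, the between-arm analysis is fixed as follows: "The magnitude of change both within and between the intervention and control groups will be assessed using mixed-model ANOVA". The same section adds "Specific demographic factors of interest (including but not limited to, gender, age, education, BMI and employment) will be adjusted for in all models" and removes participants with missing values from the repeated-measures models.

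Sample size uses the same test. It is described as "2 groups, each with 2 time points", with a "small-medium, within-between, interaction effect (Cohen’s *f* = 0.15", and the required number "at the 5% level of significance and 80% power was 90, or 45 per group".

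The data collection section confirms that the arms share only two time points: "Control participants were surveyed at two time points: 6 weeks prior to program commencement (CT1) and on entry to the program (CT2". Primary and secondary outcomes describes the confidence items as "presented on a 5-point Likert confidence scale" and says that primary and secondary measures alike are examined as change over time and between groups.

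Assignment of groups states that the class day the participant picked decided the arm.

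**The concern.** With two time points and complete cases, the group-by-time F test is algebraically the two-sample t test on T2 minus T1. With demographic covariates it becomes a regression of that change on group and those factors. Either way the T1 score enters with its slope fixed at 1. The open-ended covariate list does not alter this, because it is a list of demographic factors and the T1 value of the outcome is not one.

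Two things are at stake.

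- **Precision.** Fixing the slope at 1 wastes information whenever the T1–T2 correlation is below 1, provided the arms have the same expected baseline.
- **Dependence on one assumption.** Arms formed by chosen class day may start apart. The change score is then right only if the gap would have persisted without the program. The plan has no second analysis to show whether the conclusion rests on that.

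**Working it through.** **Inputs.** From Sample size: f = 0.15, two groups, two time points, 5% level, 80% power, N = 90. The T1–T2 correlation (rho) is not stated and is treated as an assumption.

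**1. Reproduce the plan's figure.** For the within-between interaction in G*Power's default form, the noncentrality is lambda = N × m × f² / (1 − rho), with m = 2 and df (1, N − 2).

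- At rho = 0.5: 90 × 2 × 0.0225 / 0.5 = 8.1 on (1, 88) df, giving power 0.804. Ninety is the smallest even N that reaches 80%.
- The N required at rho 0, 0.3, 0.4, 0.6, 0.7 and 0.8 is 178, 126, 108, 72, 56 and 38. Of the values tried, only 0.5 returns 90.
- On this scale f = 0.15 is a between-arm difference in mean change of 4 × 0.15 = 0.60 single-time-point SD.

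**2. Compare the two analyses when expected baselines are equal.** In SD² units, the variance per person is 2(1 − rho) for the change score and 1 − rho² for T2 adjusted for T1. With 45 per arm, lambda = 0.36 × 90/4 divided by that variance, on 88 and 87 error df.

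| rho | Variance, change | Variance, adjusted | Power, change | Power, adjusted |
|---|---|---|---|---|
| 0.3 | 1.40 | 0.91 | 66% | 84% |
| 0.4 | 1.20 | 0.84 | 73% | 87% |
| 0.5 | 1.00 | 0.75 | 80% | 90% |
| 0.6 | 0.80 | 0.64 | 88% | 94% |
| 0.7 | 0.60 | 0.51 | 95% | 98% |

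At rho = 0.5 the lambdas are 8.1 and 10.8. A simulation of 20,000 runs gave 0.803 and 0.898.

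**3. Let the arms start apart by d = 0.2 SD, with rho = 0.5.**

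- *Stable gap* (it would still be 0.2 SD at T2 with no program). The change score is unbiased. The adjusted estimate is off by d(1 − rho) = 0.2 × 0.5 = 0.1 SD. Its variance is 0.75 × (4/90) × (1 + 0.04/4) = 0.0337. With no true effect, lambda = 0.01/0.0337 = 0.30 and the false-positive rate is about 8.4%. With a true 0.6 SD effect and the intervention arm starting lower, lambda = 0.25/0.0337 = 7.4 and power is about 77%, below the 80% of the change score.
- *Gap that regresses to a common mean* (it would be 0.1 SD at T2). The adjusted estimate is unbiased and keeps 5%. The change score is off by 0.1 SD in the opposite direction. Its variance is 4/90 = 0.0444, so lambda = 0.01/0.0444 = 0.225 and the false-positive rate is about 8%.
- *Mean squared error under the stable gap.* Adjusted: 0.0337 + 0.01 = 0.0437. Change score: 0.0444. The two are about level at 0.2 SD; a larger stable gap favours the change score.

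**The case against.** The strongest reply is that the 80%-to-90% comparison belongs to a randomised trial, and this is not one. The Discussion itself says true randomisation was not possible. If the arms are stably different groups, the change score is the unbiased analysis and baseline adjustment brings in the bias, as step 3 shows. The stated interest is change, and the planned model addresses it directly. Sample size and analysis agree with each other, and the planned test delivers the power it claims. All of this stands. It rules out presenting baseline adjustment as simply better.

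The practical stake may also be small. The protocol calls f = 0.15 conservative against an earlier evaluation that reported d > 0.8. If the between-arm difference in change were 0.8 SD at rho = 0.5, lambda would be 0.64 × 90/4 = 14.4 for the change score and 14.4/0.75 = 19.2 adjusted, giving about 96% and 99% power.

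A reader might infer four stronger points that the document does not support:

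- *The primary analysis is wrong or underpowered.* It is neither. It reproduces its 80%.
- *Self-selection biases the change score in particular.* Which analysis is biased depends on whether a baseline gap persists or regresses, and the document does not say.
- *Adjustment would remove ceiling effects on the 5-point items.* A linear model does not do that, and no baseline distribution is given from which to judge a ceiling.
- *Fewer completers would suffice.* That holds only with equal expected baselines, and recruitment ended on 1/11/18.

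The objection does not justify relying on the change score alone. Since the document does not settle which assumption holds, one analysis cannot show how far the result depends on it.

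**Conclusion.** The point holds as a cheap improvement to a valid plan. The group-by-time ANOVA compares change scores, never uses the T1 score as a covariate, and rests on a single assumption about baseline differences.

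If the arms have equal expected baselines, adjusting T2 for T1 raises power at N = 90 from about 80% to 90% at rho = 0.5. The range is 66% to 84% at rho 0.3 and 95% to 98% at rho 0.7. These figures assume a 0.60 SD effect and equal arms of 45. They allow neither for gains from the demographic covariates nor for the multiplicity correction.

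If the arms do not have equal expected baselines, either analysis can be off by gap × (1 − rho), about 0.1 SD for a 0.2 SD gap at rho = 0.5. That is one-sixth of the design effect. For the secondary outcomes the size of any gain is unknown, because no correlations are given.

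**What to change.** Add to Statistical methods: for each cooking-confidence item, and for each secondary outcome measured at T1 and T2 in both arms, fit a linear model of T2 on group, the T1 value of that same outcome and the planned demographic factors. Report the adjusted group difference with a 95% CI next to the group-by-time ANOVA.

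State in advance which of the two is primary. Report the baseline difference between arms for each outcome. Treat a between-arm conclusion as robust only if both analyses agree; where they differ, interpret the result in light of the baseline difference. The three-time-point analysis within the intervention arm is unaffected.

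The cost is one or two sentences and some further SPSS output, with no new data or participants. The downside is a second set of estimates that may differ from the first if the arms start apart, which is why the primary analysis must be named beforehand.

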### Assignment of groups

Subsequent sampling for the control and intervention groups was purposive from the program registration database. Classes were offered on all days of the week except Sunday and the day chosen by the participant determined their allocation to either the control group or the intervention group. If a subject met the inclusion criteria of being 18 years and above and selected a class on either a Monday or a Thursday, they were eligible to become a control participant. Intervention participants were those who met the inclusion criteria of being 18 years and above and selected a class on any of the other days of the week. This sampling approach and allocation of registered people to the two groups was, therefore, pseudo-random and chosen to fit in with the design and philosophy of the program, which emphasises the importance of participants attending the program when and with whom they want.

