#### Intervention

The intervention involved participation in one of the nineteen 7-week cooking programs that were delivered at six metro and two regional locations throughout WA from the fully equipped JMOF mobile kitchen. Each program involved a 1½ hour hands-on cooking session held once per week for 7 weeks. The weekly sessions were scaffolded in their recipe complexity to enable increased cooking confidence, skill development and food literacy knowledge. Classes were delivered by a JMOF-trained, qualified nutritionist who demonstrated the recipe of the day which participants then cooked for themselves in groups of four to a workstation. Each week there was a new “Jamie” recipe and over the course of the program participants learnt to cook dishes from every mealtime i.e. breakfast, lunch, dinner and side dishes. As well as learning cooking skills, the participants were taught knife handling as well as how to bring out the best flavours from fresh foods and how to create dishes without using pre-prepared ingredients. They were also taught how to plan a food budget to help reduce food waste and be more economic in the kitchen. Assessments for the Intervention group were undertaken just prior to their program start date, immediately after their program was completed and 6 months after completion (Fig. 2).

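### Each class lies wholly in one arm, yet the power calculation and ANOVA treat participants as independent, so positive within-class correlation would make the group-by-time test too liberal

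*Protocol article*

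**What the plan says.** **Allocation.** Under Assignment of groups, "the day chosen by the participant determined their allocation to either the control group or the intervention group". Adults choosing a Monday or Thursday class could become controls; those choosing any other day except Sunday, when no classes ran, were intervention participants. A class therefore belongs entirely to one arm. The same section gives the reason for this scheme: the program values people "attending the program when and with whom they want".

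**Delivery.** Under Intervention, a nutritionist demonstrates a recipe to the class and "participants then cooked for themselves in groups of four to a workstation", weekly for seven weeks. There were 19 courses at eight locations. Under Study design, controls come from the same locations. Under Control and under Data collection schedule and measures, controls are assessed before the program and on entry to it.

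**Sample size.** The design is "2 groups, each with 2 time points", and the required total "at the 5% level of significance and 80% power was 90, or 45 per group". No design effect is mentioned.

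**Analysis.** Under Statistical methods, "The magnitude of change both within and between the intervention and control groups will be assessed using mixed-model ANOVA", with adjustment for demographic factors such as gender, age and education. Read with the Sample size section, mixed-model here means group (between) by time (within). It does not mean a random effect for class.

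**The concern.** The error term of a group-by-time ANOVA takes each participant's change as independent of everyone else's. Here the class is nested in arm, so anything that makes classmates change alike adds variance to the arm difference that this error term does not carry. Two routes are plausible. Shared teaching can make changes alike in the intervention arm. Choosing one's own class, perhaps with companions, can do so in either arm.

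With positive correlation, the p-values and intervals for the primary comparison are too optimistic, and the stated power is too high. The planned false-discovery-rate correction works from those same raw p-values, so it does not repair them. Because the article names both the model and the sample-size design, this is a stated choice and not a detail left to an analysis plan.

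**Working it through.** **1. Reproduce the plan's figure.** Inputs from the Sample size section: f = 0.15, two groups, two time points, alpha 5%, power 80%. Assumption: correlation between time points 0.5 (the usual G*Power default; the article does not state it).

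- Noncentrality = f² × N × 2 / (1 − 0.5) = 0.0225 × 90 × 2 / 0.5 = 8.1, with 1 and 88 degrees of freedom. Power is 80.4% at N = 90 and 79.5% at N = 88, so 90 reproduces.
- Recruitment: 90 / 0.55 = 163.6, giving 164, as stated.
- Equivalent standardised difference in change: √(4 × 8.1 / 90) = 0.6.

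Both figures reproduce with a design effect of exactly 1, that is, with independent participants.

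**2. Formulas with clustering.**

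- Equal class size m: D = 1 + (m − 1) × ICC. If sizes vary by chance (Poisson), D = 1 + mean size × ICC.
- With equal arms, the variance of the arm difference is multiplied by the average of the two arms' D values. If only the intervention arm is clustered, this is (1 + D) / 2.
- Actual type I error of the nominal 5% test = 2 × [1 − Φ(1.96 / √D)].
- Power of an analysis with a correct standard error: two-sample t test, difference 0.6, effective n = 45 / D per group.

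**3. Assumptions.** The article gives neither the ICC of change nor the number analysed per class. I take ICC 0.02 to 0.10 and two class-size settings.

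- *Sparse classes.* If every course ran one class on each of six days, there were 19 × 2 = 38 control and 19 × 4 = 76 intervention classes. At 45 per group the mean analysed class size is 45/38 = 1.18 and 45/76 = 0.59. The averaged D is 1 + 0.89 × ICC.
- *Fuller classes.* 4 to 8 analysed per class. At 45 per group this means only about 6 to 11 classes per arm (45/8 and 45/4).

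**4. Results.**

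| Analysed per class | Arms clustered | ICC | Design effect | Type I error | Power, 45 per group |
|---|---|---|---|---|---|
| about 1 | both | 0.02 | 1.018 | 5.2% | 80% |
| about 1 | both | 0.10 | 1.089 | 6.0% | 77% |
| 4 | intervention only | 0.02 | 1.03 | 5.3% | 79% |
| 8 | intervention only | 0.10 | 1.35 | 9.2% | 67% |
| 4 | both | 0.02 | 1.06 | 5.7% | 78% |
| 8 | both | 0.10 | 1.70 | 13.3% | 57% |

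Example, last row: 1.96 / √1.70 = 1.503, two-sided tail 13.3%; effective n = 45 / 1.70 = 26.5 per group.

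**5. Site differences.** A stable site effect enters both time points and cancels in the change. A site-specific change biases the arm contrast only if the arms are spread differently over sites. A null simulation with eight sites agrees. With the intervention share running from 20% to 80% across sites, stable differences gave a bias of about 0.00 SD in group by time, and site-specific changes of −0.3 to +0.3 SD gave 0.15 SD. With balanced shares the same changes gave 0.00.

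**The case against.** The strongest reply concerns size. With 45 per group spread over 19 courses and six class days, most classes may hold about one analysed person, and there is then little within-class correlation to ignore. This stands: in that setting the test runs at 5% to 6%. If many more people enrolled, classes would be fuller, but power would no longer be that of 45 per group.

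Controls are also measured before any teaching, so a shared trainer or workstation cannot correlate their changes. That stands too. Clustering of controls rests on self-selection alone, and the article states a philosophy of attending with chosen companions without saying how often this happened.

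A further reply is that the covariate list is open-ended. That helps little: the list concerns demographic factors, and an added individual covariate does not model correlation within a class.

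Three stronger readings are tempting, and the documents do not support them:

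- *That 13% type I error and 57% power are the expected size.* They need the highest assumed ICC, the largest assumed classes and clustering in both arms at once. No source is given for 4 to 8 analysed per class.
- *That omitting course and location also shrinks the standard error and leaves site differences in the comparison.* Both arms were drawn from the same locations, so location is crossed with arm. Leaving out a balanced blocking factor tends to make the standard error too large, and stable differences cancel. The article shows no imbalance of arms by site.
- *That intervention-only Saturday classes are part of this problem.* They raise a question of self-selection, not of clustering. The article concedes that true randomisation was not possible and adjusts for employment, a plausible correlate of choosing Saturday.

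**Conclusion.** The point holds in direction. Allocation and teaching are by class, while the stated sample size and model assume independent participants, so any positive within-class correlation of change makes the group-by-time standard error too small.

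The size is unknown and may be small. It runs from about 5% to 6% type I error with sparse classes, through 5.3% to 9.2% with 4 to 8 per class clustered in the intervention arm only, to an upper scenario of 13% with both arms clustered. All of these rest on the assumed ICC range of 0.02 to 0.10 and on assumed class sizes. Bias from sites is conditional: it needs course- or location-specific change together with an unequal arm mix. The plan should be changed because the primary p-value is affected and the remedy is cheap.

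**What to change.** Keep the group-by-time comparison, and change the basis of inference:

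- Use standard errors that are cluster-robust by class (course by class day), with a small-sample correction. Where classes hold enough analysed people, a linear mixed model with a random class-by-time term and Satterthwaite degrees of freedom is an alternative. With about one person per class, that variance is barely separable from residual error, so the robust version is safer.
- Include location (eight levels) crossed with time, or course as a random effect. Avoid 19 fixed course levels crossed with time, which would use 18 degrees of freedom among about 90 analysed people.
- State under Sample size that 80% power at 45 per group assumes no within-class correlation. Report the analysed class sizes and the estimated ICC.
- Optionally, repeat the analysis without Saturday classes as a separate check on self-selection.

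Cost: analysis wording only, since class day was taken from the registration database to assign the arms. Intervals become somewhat wider, and location crossed with time uses up to 7 degrees of freedom.

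### Adjusting the within-group time tests for age and BMI removes no confounding and, if both are entered as measured in SPSS repeated-measures GLM, tests change at age 0 and BMI 0

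*Protocol article*

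**What the plan says.** All the relevant text is in the protocol article, under Statistical methods.

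- Software: "IBM SPSS Statistics for Windows version 25.0".
- Six-month analysis, intervention arm only: "changes within the intervention group will be assessed across three time points IT1, IT2 and IT3 using repeated-measures ANOVA".
- Comparison with controls: "The magnitude of change both within and between the intervention and control groups will be assessed using mixed-model ANOVA".
- Covariates: "including but not limited to, gender, age, education, BMI and employment) will be adjusted for in all models".
- Anyone with a missing outcome or predictor is dropped from the repeated-measures models.

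The section is silent on whether age and BMI are continuous or banded, whether they are centred, which SPSS procedure is used, and whether change is read from the omnibus time F or from marginal means.

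Under Sample size, only the group-by-time comparison is powered ("2 groups, each with 2 time points"). The article says there that T3 was not powered, because the interest is in whether the effect lasts.

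**The concern.** The adjustment rule covers all models, so it also covers the IT1-IT3 model in a single arm and the within-group part of the mixed ANOVA. In a within-person comparison each participant is their own control. A fixed covariate such as age cannot confound the mean change, so the adjustment gives no protection against bias there.

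It can do harm. When covariates are added, SPSS's repeated-measures GLM by default regresses each time contrast on them and tests the intercept as the time effect. The intercept is the expected change when every continuous covariate equals zero. With age in years and BMI in kg/m² as measured, that point lies far outside a sample aged 18 or over. The question the article asks is whether the mean outcome changes. The F would answer a different one, very imprecisely.

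Controls have no T3 survey, so the IT1-IT3 model is the only stated inferential analysis of the 6-month questionnaire and clinical data. A real change could be reported as non-significant. If change depends on age, a significant result could appear with no mean change.

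**Working it through.** **1. The article's own figure.** For a 2 × 2 interaction, λ = f²·N·m/(1 − ρ), with df 1 and N − 2. Inputs from Sample size: f = 0.15, N = 90, m = 2. The correlation is not stated; ρ = 0.5 is assumed.

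λ = 0.0225 × 90 × 2 / 0.5 = 8.1, giving power 0.804. This reproduces "at the 5% level of significance and 80% power was 90, or 45 per group". Allowing for 55% retention, 90 / 0.55 = 163.6, so 164. Both stated figures hold.

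**2. Inputs for the three-visit time test.**
- From the article: 45 (required per group) and 87 (target at each of T1 and T2 in the intervention arm). No T3 number is given, so both are used as possible numbers with complete data.
- From the article: benchmark change above 0.53 points, with d above 0.8, which implies an SD of about 0.53 / 0.8 = 0.66.
- Assumed, because the article gives none of them: age 45 (SD 15), BMI 28 (SD 5.5), age and BMI uncorrelated, between-visit correlation 0.5, change unrelated to age and BMI, and the same change at IT2 and IT3.

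**3. Variance of the intercept with covariates as measured.** Relative to centred covariates it is multiplied by about 1 + (mean age/SD)² + (mean BMI/SD)²:

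1 + (45/15)² + (28/5.5)² = 1 + 9 + 25.9 = 35.9, so the standard error is about √35.9 = 6.0 times larger.

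**4. Power at the 5% level.** For the profile (0, d, d) in SD units, the sum of squares about its mean is (2/3)d². So λ = n·(2/3)d²/(1 − 0.5), divided by 35.9 when covariates are uncentred; df are 2 and 2(n − 3).

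| Change | n | λ centred | Power centred | λ uncentred | Power uncentred |
|---|---|---|---|---|---|
| 0.6 SD | 45 | 21.6 | 99% | 0.60 | 10% |
| 0.6 SD | 87 | 41.8 | 100% | 1.16 | 15% |
| 0.8 SD | 45 | 38.4 | 100% | 1.07 | 14% |
| 0.8 SD | 87 | 74.2 | 100% | 2.07 | 23% |

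Simulation of the same test agrees within about one to two percentage points.

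**5. Range over other assumptions, for the 0.53-point change.**

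| Age (SD) | BMI (SD) | SE multiplier | Uncentred, n = 45 | Uncentred, n = 87 |
|---|---|---|---|---|
| 50 (12) | 27 (5) | 6.9 | 11% | 18% |
| 45 (15) | 27 (5) | 6.3 | 13% | 21% |
| 45 (15) | 28 (6) | 5.6 | 15% | 25% |
| 40 (18) | 28 (7) | 4.7 | 20% | 35% |

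Centred power is about 100% in every row. For a smaller change of 0.20 points it is 52% (n = 45) or 83% (n = 87) centred, against 6-9% uncentred.

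**6. False rejection when the mean change is zero but change varies with age.** With an assumed slope of 0.015 points per year and mean age 45, the implied change at age 0 is −0.015 × 45 = −0.675 points, although the average participant does not change. In simulation with n = 87 (BMI 27, SD 5) the uncentred test rejects 32% of the time, the centred test 7%. With a slope of 0.3 SD per SD of age, rejection is 15-28% uncentred for n = 45 to 87, against about 6% centred.

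**7. What does not move.** Centring alters the intercept, not the group coefficient in a model for change. Simulated group-by-time power was 0.8035 both ways, so N = 90 and the target of 164 stand.

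**The case against.** The strongest reply is that nothing in the article says the covariates will be left uncentred, and that covariate coding is a detail a condensed article commonly leaves to the full protocol or analysis plan. That is right as far as it goes. A reader might infer that the plan fixes an uncentred analysis; the text does not support this. The problem needs age and BMI as raw continuous values, the repeated-measures GLM procedure, covariate-by-time terms, and change judged from the omnibus time F. Dropping incomplete cases fits that procedure, but the article does not name it. Banded covariates, a mixed model with covariate main effects only, or marginal means evaluated at covariate means would each avoid it.

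A reader might also infer that the primary comparison is undermined, or that every endpoint loses almost all power. Neither follows. The group-by-time test is unchanged, microbiota composition has its own multivariate analysis, and for the benchmark effect some 11-35% power remains even in the bad case. The distributions behind these figures are assumed, and the over-rejection depends on an assumed slope.

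Finally, the article says T3 was not meant to detect a change. But maintenance is still to be examined through the IT1-IT3 repeated-measures ANOVA, whose time contrasts share the same intercept.

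What survives is the stated scope of the rule. Demographic adjustment is expressly extended to all models, including a single-group test where it removes no confounding and where default execution gives the wrong null hypothesis. That is a stated choice, not only a missing detail.

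**Conclusion.** The point holds conditionally. The article requires age and BMI adjustment in within-group time tests that do not need it for bias. If both are entered as measured in the default SPSS procedure, the time F concerns a person of age 0 and BMI 0. Under age 45 (SD 15), BMI 28 (SD 5.5) and correlation 0.5, power for a 0.6 to 0.8 SD change drops from about 99-100% to about 10-23%. Over wider assumptions it is roughly 11-35% for the 0.53-point change. Over-rejection is possible when change varies with age.

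The consequence is confined to the IT1-IT3 time test and the within-group part of the mixed ANOVA. It is worth correcting before analysis, because T3 has no power calculation that might expose the loss.

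**What to change.** Amend the adjustment sentence under Statistical methods along these lines:

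*Within-group time tests, including the IT1-IT3 repeated-measures ANOVA, will be unadjusted or will use continuous covariates centred at the mean of the analysed sample. Demographic adjustment applies to the group-by-time comparison.*

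The cost is one sentence and, if centring is chosen, one recoding step after incomplete cases are dropped. No new data and no change to the sample size are needed.
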